### Shared learning opportunities through site visits

Practices randomized to the shared learning intervention arm are offered the opportunity to visit an exemplar practice with a particularly strong or innovative approach to QI. Exemplars are identified through nominations from facilitators and other members of the H2N collaborative. They may or may not be practices enrolled in H2N but must be within the three state geographic region of the study. Exemplars are screened by phone about their QI program and asked for reports on their clinical performance measures. Practices randomized to visit an exemplar receive support to coordinate the site visit and travel reimbursement. Each exemplar practice hosts 4–6 practices for a half-day visit within the 4-month intervention period. The goal of the site visit is to create an opportunity for practices to directly observe their QI approach and tools, examine work flows and team member roles, and develop an on-going relationship with a practice that has an innovative approach to QI.

### Educational outreach

The purpose of the academic educational outreach is to encourage use of a CVD risk calculator or estimator [19] within patient encounters. Current evidence-based clinical guidelines support the use of such a risk estimator to inform decisions about use of a statin medication to manage CVD risk based on age, gender, smoking and diabetes status, lipoprotein levels, and blood pressure [20]. A small advisory group of full-time primary care clinicians are developing the content of the educational outreach program to address priority topics and issues. The educational outreach will begin with a brief introductory video example of how a CVD risk estimator can be integrated into a patient visit. This will be followed by a 30-min phone call between each clinical team in practices randomized to the intervention and a physician academic expert. Each academic expert will be assigned 15 to 20 practices for a phone call.

### Data collection and measures

Sources of data, measures, and variables are listed in Table 2. A single practice-level survey and a survey completed by all clinicians and practice staff are administered at baseline, 4 months after the period of the enhanced practice support and 6 months after withdrawal of all practice support activities. The practice survey includes practice demographics, information about health IT systems, and the Change Process Capacity Questionnaire (CPCQ), a measure of the ability of an organization to manage change processes [21]. The staff member survey includes the adaptive reserve scale, a measure of internal capability for organizational learning and development [22].

**Table 2 Tab2:** Measures and data sources

Construct	Data source	Measure(s)	Timing
Practice capacity for quality improvement (QI)	Quality improvement capacity assessment (QICA) survey	• Eight change concepts (see Table 1)	Baseline and 9–12 months after start of practice facilitation
Prior experience with QI	Practice survey	• Change process capacity questionnaire (CPCQ) [21]	Baseline and 4 months after exposure to enhanced support interventions
External organizational support for QI	Practice survey	• Is the practice is part of a large organization with a centralized QI team? • The autonomy of the practice to choose what QI projects they wish to work on	Baseline and 4 months after exposure to enhanced support interventions
External climate for QI	Practice survey	• Location of practice: Washington, Oregon, or Idaho	Baseline and 4 months after exposure to enhanced support interventions
Adaptive reserve	Staff survey	• Adaptive reserve scale [22]	Baseline and 4 months after exposure to enhanced support interventions
Clinical quality measures for ABCS CVD risk factors	Numerator and denominator report generated by each practice from their Electronic Health Record	• NQF0068: ischemic vascular disease: appropriate use of aspirin/antithrombotic • NQF0018: controlling high blood pressure • NQF0028: preventive care and screening: tobacco use • CMS proposed statin measure	Every 90 days with a 12 month look-back period

*CVD* cardiovascular disease; *NQF* National Quality Forum; *QI* quality improvement; *ABCS* aspirin, blood pressure, cholesterol, and smoking

CVD clinical quality measures (CQMs) on each of the ABCS risk factors are being submitted by each practice every 3 months with a 12-month look-back period for each submission. Each practice submits a numerator and denominator for each CQM every 90 days. Three of the CQMs are based on definitions provided by the National Quality Forum (NQF): NQF0068: ischemic vascular disease: appropriate use of aspirin/antithrombotic [23]; NQF0018: controlling high blood pressure [24]; and NQF0028: preventive care and screening: tobacco use: screening [25]. The original NQF cholesterol measure proposed for the study is under revision based on recent changes in evidence-based clinical guidelines. Instead, we are requesting data from each practice on the proportion of patients prescribed a statin who (a) have diabetes; (b) have a history of ischemic vascular disease; or (c) in the absence of either condition have a low-density lipoprotein (LDL) value greater than 190 mg/dl [26].

Practice capacity for QI activities are measured at two time points by the quality improvement capacity assessment (QICA) tool, a practice self-assessment tool used by the facilitators to help practices identify areas where change is needed to improve their capacity to engage in QI. It is a modification of a previously validated tool used to guide primary care practice transformation into a medical home [16]. The single QICA for each practice is completed by the practice team as a group during the first face-to-face visit with their facilitator and again at the fourth of the five face-to-face quarterly visits.

External organizational support for QI is reflected in the growing influence of individual practice relationships with other practices, hospitals, and healthcare systems. Two questions on the practice survey are used to assess this external organizational support: the degree to which the practice is part of a larger organization with a centralized QI team and the autonomy of the practice to choose what QI projects they wish to work on.

External climate for QI is indicated by the state within which the practice is located. Washington, Oregon, and Idaho all provide unique state contexts and history with primary care support, transformation, innovation, and medical home work. For example, Oregon is currently a site for the CMS/CMMI Comprehensive Primary Care Initiative. Washington and Idaho both received a State Innovation Model grant in 2014 from CMS. Idaho is supporting primary care medical homes as part of their SIM grant, but not Washington.

Qualitative data: We are using observation, interviews, and field notes to describe how delivery of QI support through PF was tailored to individual practices, the influence of the external climate, as well as challenges, success factors, and lessons learned. Practice facilitators are keeping detailed notes after each contact with their assigned practices including face-to-face visits, phone calls, emails, and text messages. In addition to these field notes, additional data are being collected through focus groups with facilitators at training sessions, interviews with experts in state level healthcare policy, and interviews with individual facilitators.

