### Practice support interventions

PF support is provided to all sites upon enrollment in the study for 15 months as a unifying approach. Two enhanced practice support interventions, shared learning through site visits and educational outreach on CVD risk calculator use, are being offered to those practices randomized to receive them over a period of 4 months approximately 3–9 months after the start of the PF support. A description of each type of external practice support follows.

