#### Data analysis

The primary aim of this study is to compare the effectiveness of adding shared learning opportunities, educational outreach, or both to PF on CQMs for each ABCS risk factor by building QI capacity within each practice. To address this aim, our primary outcome is the practice-level blood pressure CQM covering the time period 1-year after intervention uptake. Specifically, all practices participating in the study are randomized to one of four intervention groups in August 2016. We define baseline ABCS CQMs as those covering the year prior to randomization (July 1, 2015 to June 30, 2016) (Fig. 2). After randomization, roll-out of the active intervention arms occurs from September 2016 to December 2016. CQM data that covers this roll-out time period for all intervention arms will not be used for outcome assessment to allow for active intervention uptake (similar to a wash-out period in a standard cross-over randomized trial). Our 1-year follow-up outcome measure for our primary aim is the blood pressure CQM that covers the 12-month time period after the intervention roll-out period, from January 2017 to December 2017.

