Our analyses will assume intention to treat principles by treating intervention assignment as randomized regardless of whether the intervention had uptake within the practice. We will also attempt to obtain outcome data for all practices even if they stop participating in the intervention. However, there may be some practices that drop-out and stop providing follow-up data. To account for bias due to loss-of-follow-up, we will adjust for baseline practice-level variables that we a priori expect to be related to outcome and may be predictive of loss-to-follow-up. Sensitivity analysis including last value carry forward (follow-up outcome is the baseline outcome for missing practice data) will also be conducted. If loss-to-follow-up is large (>15 %), we will further explore inverse probability of treatment weighting or multiple imputation to handle missing outcome data. We will further conduct subgroup analyses to assess for differential intervention effects (moderators) by baseline practice-level variables including PF support organization, prior practice experience obtaining customized data to drive improvement, prioritization of the work by the practice (high, low), and adaptive reserve (low, medium, and high). Similar analysis will be conducted for secondary outcomes including the other ABCS CQM measures and changes in practice variables such as practice capacity QI.

If we find a difference between any of the four intervention arms, we will conduct a mediator analysis to assess if change in practice capacity for QI was a potential pathway for change in ABCS CQM outcomes. Specifically, we will conduct a mediator analysis following the Barron and Kenny framework [27]. Step 1 is to show that the intervention had an effect of the follow-up outcome. Step 2 is to show that the intervention was associated with change in the potential mediator practice capacity for QI. Step 3 is then to show that the intervention effect is mediated or reduced once the mediator is taken into account. For step 2, we will use a similar linear regression model as outlined for the primary analyses, but the outcome will be the mediator change in practice capacity for QI. For step 3, we will use a similar linear model as outlined for the primary analysis except now further adjust for the change in practice capacity for QI. We will use the method of Sobel [28] to test for the mediator’s indirect effect of the interventions on the ABCS CQM outcome.

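### The second QICA is timed from the start of practice facilitation rather than from exposure, so in early-starting practices it can precede the support it should mediate; the Sobel test then adds conservatism

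*Protocol article*

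**What the plan says.** - **Mediator.** Under Data collection and measures, the practice team completes the QICA at the first facilitator visit and "again at the fourth of the five face-to-face quarterly visits". Table 2 gives the timing as "Baseline and 9–12 months after start of practice facilitation". Change in this score is the mediator in the Data analysis section.
- **Exposure.** Practice support interventions says "PF support is provided to all sites upon enrollment in the study for 15 months". Enhanced support is offered "over a period of 4 months approximately 3–9 months after the start of the PF support". Data analysis gives one calendar window for every practice: "roll-out of the active intervention arms occurs from September 2016 to December 2016".
- **Other measures.** Table 2 times the follow-up practice and staff surveys at 4 months after exposure to enhanced support. Of the capacity-related measures in that table, only the QICA is timed from PF start.
- **Analysis.** "If we find a difference between any of the four intervention arms, we will conduct a mediator analysis". It follows a three-step framework whose first step is an effect on the outcome. For the indirect effect: "We will use the method of Sobel".
- **Status.** The Background section makes mediation by QI capacity part of the primary hypothesis.

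**The concern.** A mediator has to be measured after the exposure whose effect it carries. Here the two run on different clocks: the QICA on each practice's own PF clock, the enhanced support on a shared calendar. Nothing in the protocol requires the second QICA to follow the practice's site visit or outreach call. Where it comes first, the QICA change in an enhanced-support practice reflects facilitation alone, as it does in the PF-alone arm. The estimated arm effect on QICA, and with it the indirect effect, is then diluted toward zero. A null mediation result could not be told apart from a mediator measured too early. The Sobel test treats a product of two coefficients as normal and so lowers the chance of detecting whatever indirect effect remains.

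**Working it through.** **1. Months on the PF clock.** Let S be the months from PF start to the opening of the support window, and Q the month of the second QICA. Read S as 3 to 9. The window is 4 months long, so it closes at S + 4, that is month 7 to 13. Table 2 puts Q at 9 to 12. The two ranges overlap.

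**2. Calendar.** Put the opening at 1 September 2016.

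| PF start | Second QICA (months 9–12) | Relation to roll-out |
|---|---|---|
| December 2015 (S = 9) | September to December 2016 | inside the window |
| March 2016 (S = 6) | December 2016 to March 2017 | last month of the window or later |
| June 2016 (S = 3) | March to June 2017 | after the window |

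The earliest Q is 9 and the latest S is 9, so the QICA never precedes the opening of the roll-out. It can precede only a practice's own exposure within it.

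**3. Share measured before own exposure.** Assume S uniform on 3–9 and exposure at S + U, with U uniform on 0–4. For fixed Q the gap Q − S is uniform over 6 months, and a practice is affected when U exceeds the gap.
- Q = 9: (1/6) × ∫₀⁴ (4 − d)/4 dd = (1/6) × 2 = 33%.
- Q = 12: (1/6) × ∫₃⁴ (4 − d)/4 dd = (1/6) × 0.125 = 2%.
- Q uniform on 9–12: the average of (13 − Q)²/48 is (64 − 1)/(3 × 144) = 63/432 = 15%.

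Simulation gave the same three values. Both month 9 and month 12 are open, because five quarterly visits may fall at months 0–12 or 3–15.

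**4. Other reading.** If the whole 4-month window lies within months 3–9, S is 3 to 5, the window closes by month 9 and the share is 0%. With a common September opening, this requires every PF start to fall between about April and early June 2016.

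**5. What dilution does.** If a share p of practices is measured before exposure, the expected arm effect on QICA falls to (1 − p) of its value: 0.67 at p = 33%, 0.85 at 15%, 0.98 at 2%. In one simulation (50 per arm, assumed arm effect on QICA 0.5 SD, mediator–outcome correlation 0.3, total effect 0.114), ungated Sobel power was 59% with no practice affected, 45% with 12.5% affected and 26% with 33% affected.

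**6. Sobel in the planned model.** Three arm indicators, 50 practices per arm, one arm's indirect effect, assumed paths 0.4 SD and 0.2, mediator and outcome residual SD 1.
- Path a: SE = √(2/50) = 0.20, z = 0.4/0.20 = 2.0.
- Path b: SE ≈ 1/√200 = 0.071, z = 0.2/0.071 = 2.8.
- Joint significance: power about 0.52 × 0.81 = 42%; by simulation 40%.
- Sobel: expected statistic 1/√(1/2.0² + 1/2.8²) ≈ 1.6, below 1.96; by simulation 20%.
- With no arm effect on the mediator (second path 0.25), rejection is about 2% for Sobel and 5% for joint significance.

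**7. The plan's own figure.** The protocol states no power for mediation. Its 80% for the omnibus F test at a difference of 0.114 reproduces: residual SD 0.26 × √(1 − 0.6²) = 0.208, 50 per arm, alpha 0.05 assumed, power 80.6%. The sample size is not in dispute.

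**The case against.** The strongest reply is that the timing problem depends on how one phrase is read. If 3–9 months bounds the whole support period, the second QICA follows exposure everywhere. If the fourth visit falls at month 12, the affected share is 2% even on the less favourable reading. PF start dates are not given and the timeline figure is not shown. This stands as a limit on size. It does not remove the point: the favourable reading needs PF starts within about two months across a target of 250 practices in three states, and the protocol does not say that they were.

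A reader might infer that most practices are affected, because at month 9 some 67% have the QICA before the roll-out closes (S above 5, so 4/6). That share includes practices already exposed, so it does not measure the defect.

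A reader might also take the significance gate for an error. It is step 1 of the framework the protocol names, it is prespecified, and it does not inflate type I error. It does cost power: the omnibus test has 25% power at a difference of 0.056 (an illustrative value, from the 5.6% average cited in the Background for educational outreach). That is a trade-off rather than a fault.

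The Sobel test, too, is conservative rather than invalid, and the path sizes used to show this are assumed. Its gap to joint significance varies: about 20 points on the paths in the working, 3 to 14 points in other scenarios. The direction was the same throughout.

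**Conclusion.** The point holds in a limited form. The protocol ties its only mediator measurement to PF start and its exposure to the calendar, and does not ensure their order. If 3–9 months marks the opening of the window, the second QICA precedes own exposure in 33%, 15% or 2% of practices, depending on whether it falls at month 9, across months 9–12, or at month 12. These shares assume uniform PF starts and exposure dates. The share is 0% on the other reading. The bias is toward a null indirect effect. Sobel adds to the loss: about 20% against 40% power on assumed paths in the four-arm model.

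The documents do not support reading this as a threat to the primary blood pressure comparison, to the stated sample size or to type I error. Nor do they show the QICA falling before the roll-out opens. The weakness concerns the mediation part of the primary hypothesis and should be corrected there.

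**What to change.** 1. Reconcile the timing statements in Practice support interventions, Table 2, the QICA paragraph and Data analysis. State whether 3–9 months bounds the opening or the whole of the enhanced support.
2. Require, identically in all four arms, that the second QICA be completed after the roll-out closes (December 2016) and within the 15 months of PF. The earliest starters (December 2015) remain in PF until about the start of March 2017, which leaves January and February 2017. For practices still in PF at that point, it can be paired with the 4-month post-exposure survey.
3. Where the last scheduled visit would fall by December 2016, move it slightly later. With visits at months 0–12 this applies when S is 8 or more, (9 − 8)/6 = 17% of practices under uniform starts.
4. Replace the Sobel test with a bootstrap interval for the indirect effect. Reporting that interval whether or not the omnibus test is significant is optional.
5. Do not split practices by whether the QICA preceded exposure. The PF-alone arm has no exposure date, and the split would condition on a post-randomization event.

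**Cost.** A change to facilitator scheduling, some moved visits and a few lines of analysis text. The QICA would fall at a variable PF month, although it also serves facilitators as a working tool. It would also lie inside the January–December 2017 outcome year, so mediator and outcome would overlap in time; this should be acknowledged when mediation is interpreted.

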### Randomization and data analysis

#### Randomization

We are using a stratified randomization with enrolled practices categorized into one of six strata defined by PF support organization (Qualis Health or ORPRN), prior practice experience obtaining customized data to drive improvement (yes, no), and prioritization of the work by the practice (high, low). Information on the latter two variables is collected in the baseline practice survey prior to randomization. Within each stratum, practices are randomly assigned by a computer-generated randomization scheme to one of the four intervention arms developed by the biostatistician. The evaluation/analysis team [[name]] are blinded to assignment.

#### Data analysis

The primary aim of this study is to compare the effectiveness of adding shared learning opportunities, educational outreach, or both to PF on CQMs for each ABCS risk factor by building QI capacity within each practice. To address this aim, our primary outcome is the practice-level blood pressure CQM covering the time period 1-year after intervention uptake. Specifically, all practices participating in the study are randomized to one of four intervention groups in August 2016. We define baseline ABCS CQMs as those covering the year prior to randomization (July 1, 2015 to June 30, 2016) (Fig. 2). After randomization, roll-out of the active intervention arms occurs from September 2016 to December 2016. CQM data that covers this roll-out time period for all intervention arms will not be used for outcome assessment to allow for active intervention uptake (similar to a wash-out period in a standard cross-over randomized trial). Our 1-year follow-up outcome measure for our primary aim is the blood pressure CQM that covers the 12-month time period after the intervention roll-out period, from January 2017 to December 2017.

**Fig. 2 Fig2:**
[figure not shown]
Project timeline and data collection windows

For the primary analysis to assess differences between the four intervention groups on the primary outcome practice-level proportion with blood pressure control at 1-year follow-up (blood pressure CQM), we will fit the following linear regression model:$$ {Y}_i={\beta}_0+{\beta}_1{X}_{1i}+{\beta}_2{X}_{2i}+{\beta}_3{X}_{3i}+{\beta}_{\mathrm{base}}{Y}_i^0+{\boldsymbol{\beta}}_z{\boldsymbol{Z}}_{\boldsymbol{i}}+{e}_i\ {e}_i\sim N\left(0,{\sigma}^2\right)\ i=1,\dots, N $$where *Y*
_*i*_ is clinics *i* blood pressure CQM at 1-year follow-up, *X*
_1*i*_, *X*
_2*i*_, and, *X*
_3*i*_ are three indicator variables for intervention assignment for site visit, educational outreach, or both, respectively, *Y*
_*i*_^0^ is baseline blood pressure CQM, and ***Z***
_***i***_ is a vector of other baseline covariates to adjust for differences between clinics including PF support organization (Qualis Health or ORPRN), baseline prior practice experience obtaining customized data to drive improvement (yes, no), and baseline prioritization of the work by the practice (high, low). We will use the Fisher’s protected least significant difference approach to control for multiple comparisons due to the comparison of four intervention arms. Specifically, we will first calculate an Omnibus *F* test to assess if there are any significant differences between intervention groups and only calculate pairwise comparisons if this omnibus test is statistically significant.

Our analyses will assume intention to treat principles by treating intervention assignment as randomized regardless of whether the intervention had uptake within the practice. We will also attempt to obtain outcome data for all practices even if they stop participating in the intervention. However, there may be some practices that drop-out and stop providing follow-up data. To account for bias due to loss-of-follow-up, we will adjust for baseline practice-level variables that we a priori expect to be related to outcome and may be predictive of loss-to-follow-up. Sensitivity analysis including last value carry forward (follow-up outcome is the baseline outcome for missing practice data) will also be conducted. If loss-to-follow-up is large (>15 %), we will further explore inverse probability of treatment weighting or multiple imputation to handle missing outcome data. We will further conduct subgroup analyses to assess for differential intervention effects (moderators) by baseline practice-level variables including PF support organization, prior practice experience obtaining customized data to drive improvement, prioritization of the work by the practice (high, low), and adaptive reserve (low, medium, and high). Similar analysis will be conducted for secondary outcomes including the other ABCS CQM measures and changes in practice variables such as practice capacity QI.

If we find a difference between any of the four intervention arms, we will conduct a mediator analysis to assess if change in practice capacity for QI was a potential pathway for change in ABCS CQM outcomes. Specifically, we will conduct a mediator analysis following the Barron and Kenny framework [27]. Step 1 is to show that the intervention had an effect of the follow-up outcome. Step 2 is to show that the intervention was associated with change in the potential mediator practice capacity for QI. Step 3 is then to show that the intervention effect is mediated or reduced once the mediator is taken into account. For step 2, we will use a similar linear regression model as outlined for the primary analyses, but the outcome will be the mediator change in practice capacity for QI. For step 3, we will use a similar linear model as outlined for the primary analysis except now further adjust for the change in practice capacity for QI. We will use the method of Sobel [28] to test for the mediator’s indirect effect of the interventions on the ABCS CQM outcome.

A secondary aim of this study is to assess if PF alone improves clinic-level ABCS outcomes (note that PF is given to all practices in our randomized trial population). To address this aim, we will conduct an observational study using data from our randomized study practices and control practices from the DARTNet Institute. Specifically, we will have data on practice-level ABCS outcomes 1-year prior to PF roll-out in each of our randomized trial practices and 1-year post PF roll-out. To control for potential confounding, we will match each randomized control trial practice to one or more control practices matching on practice size (clinician FTE), QI measure reporting capabilities as measures by their ability to generate a custom report without support from their EHR vendor, and rural/urban location. For each matched pair, we will use the same data ascertainment windows based on when the randomized control trial practice had PF rolled out. This will control for temporal changes. We will conduct similar analyses as proposed for the randomized trial except that now outcome time is tied to PF roll-out, and we will only include a single intervention indicator that had or did not have PF.

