### Sample size

The main aim of the trial is to assess if any of the enhanced practice support arms (site visit, educational outreach, or both) improved ABCS CQM outcome performance relative to practices that received PF alone. If one assumes a 20 % attrition rate over the life of the study leaving 50 practices in each of the four intervention arms, we have 80 % power to detect a 0.114 proportion improvement in any of the three enhanced practice support arms relative to PF for the 1-year practice outcomes blood pressure CQM or aspirin CQM. We assumed an outcome standard deviation of 0.26 for both ABCS outcomes (based on baseline data from the enrolled practices) and a *F* test comparing the four intervention arms assessing for any difference between groups. Further, we used an adjusted sample size calculation for ANCOVA models [29] (proposed analysis adjusts for baseline outcome) assuming a 0.60 correlation coefficient between baseline outcome measure and follow-up outcome measure. Even with an additional 10 % clinic attrition rate (45 practices per arm with follow-up), we will have 80 % power to detect a difference of 0.121 in practice proportion improved in either ABCS outcome. We conducted power calculations via simulation using R version 3.0.2.

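### Fisher's protected LSD gives only weak familywise control with four arms: up to about 12% over all pairs, and about 9% against PF alone if exactly one arm works

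*Protocol article*

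**What the plan says.** The Data analysis section of the protocol article fits a linear regression of the one-year practice-level blood pressure measure on "three indicator variables for intervention assignment for site visit, educational outreach, or both, respectively", with the baseline measure and the stratification variables as covariates. For multiplicity it adopts Fisher's "protected least significant difference approach to control for multiple comparisons due to the comparison of four intervention arms". The procedure is spelled out: calculate the omnibus F test, and "only calculate pairwise comparisons if this omnibus test is statistically significant". No adjustment of the pairwise step is given, and no significance level is stated.

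The Sample size section gives the main aim as to "assess if any of the enhanced practice support arms (site visit, educational outreach, or both) improved ABCS CQM outcome performance relative to practices" receiving PF alone. Power is calculated for the four-group F test. The Data analysis section applies a similar analysis to the secondary outcomes, so the same procedure carries over to them.

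**The concern.** The F gate protects the pairwise step only while all four arms are equal. Once one arm truly differs by a useful amount, the gate usually opens. Up to three equal arms then remain, and each pair among them is tested at the unadjusted level. With three groups at most one true null pair can remain after the gate opens, so protected LSD is adequate there. With four groups it is not.

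The trial is meant to show which addition to PF is worth making, and that answer comes from the pairwise step. When the trial succeeds, an ineffective support strategy could be separated from PF, or two equivalent strategies from each other, more often than the stated control for multiple comparisons suggests.

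**Working it through.** **Inputs.** From the Sample size section: 50 practices per arm after attrition, a difference of 0.114, an outcome SD of 0.26, a baseline to follow-up correlation of 0.60, a four-group F test, and a second case of 45 per arm with 0.121. Assumed: alpha 0.05 for the F test and two-sided 0.05 for each pairwise test.

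**Residual SD.** 0.26 × √(1 − 0.60²) = 0.26 × 0.80 = 0.208.

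**Reproducing the stated power.** With one arm shifted by d, the noncentrality is 0.75 × n × d² / 0.208², on 3 and 4n − 5 degrees of freedom.
- n = 50, d = 0.114: 0.75 × 50 × 0.012996 / 0.043264 = 11.26, power 80.5%.
- n = 45, d = 0.121: 0.75 × 45 × 0.014641 / 0.043264 = 11.42, power 81.0%.

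Both agree with the stated 80%, which supports the assumed alpha.

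**Familywise error of the planned procedure.** Simulation with 400,000 replicates per scenario: F test at 0.05, then unadjusted t tests with pooled variance (|t| > 1.97). The error is the chance of at least one false rejection among the pairs that are truly equal.

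| True state, 50 per arm | Gate opens | All six pairs | Three comparisons with PF |
|---|---|---|---|
| All arms equal | 5% | 5.0% | 4.0% |
| One enhanced arm better by 0.05 | 20% | about 7% | about 5.5% |
| One enhanced arm better by 0.114 | 81% | 11.8% | 8.8% |
| One enhanced arm better by 0.20 or more | about 100% | 12.2% | 9.1% |
| Two enhanced arms better by 0.114 | 91% | 9.6% | 5.0% |
| All three enhanced arms better by 0.114 | 81% | 11.8% | 0 (no true null) |

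With 45 per arm and one arm better by 0.121, the figures are 11.8% and 8.8%.

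The two-arm row can be checked by hand. Two separate null pairs remain (PF with the ineffective arm, and the two effective arms with each other), so with the gate open the error is close to 1 − 0.95² = 9.75%.

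**Direction.** The 8.8% counts false findings either way. With one arm better by 0.114, the chance that some ineffective arm is falsely declared better than PF is 4.4%, against a one-sided 2.5%.

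**Alternatives, one arm better by 0.114.**
- Closed F testing over the three PF comparisons: error 4.1 to 4.2%, and no more than about 5% in any scenario tried.
- F gate, then the Fisher-Hayter critical value (95% point of the studentized range for three groups, divided by √2, giving |t| > 2.36): 4.9% over all pairs, and about 5.0% at most across scenarios.
- Power to separate the single effective arm from PF: 0.71 with protected LSD, 0.68 with closed testing, 0.63 with Fisher-Hayter.

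**The case against.** The best defence rests on the factorial structure. The fourth arm contains both additions, so a component that works would normally work there too. Two arms then beat PF, only one null comparison with PF remains, and the error against PF is about 5%. If both components work and add up (0.057, 0.057 and 0.114), no PF null is true. The 9% against PF needs exactly one effective arm: only the combination works, or a component works alone but not in combination. This stands. It does not rescue the full set of pairs, where the error is still just under 10% with two equally effective arms and about 12% with three.

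A reader might also infer that any given ineffective strategy is declared effective at twice the nominal rate. The figures do not support that. Each ineffective arm is separated from PF in at most 5% of trials, and at the design effect in about 2.4% in the favourable direction. The inflation lies in the union over arms.

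Nor do the documents support saying that the method gives no protection. It holds 5% when all arms are equal. The stated aim asks whether any enhanced arm helps, the omnibus test addresses whether the arms differ at all, and the method is prespecified and correctly described. What remains is that it is offered as control for comparing four arms, and its pairwise step does not give strong control.

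**Conclusion.** The point holds as a lack of strong familywise control in the pairwise step. At the design difference, the error over all six pairs is about 12% with one arm, or all three enhanced arms equally, effective, and just under 10% with two. Over the three PF comparisons it is about 9% two-sided if exactly one arm works, and about 5% if a single component works alone and in combination. At a difference of 0.05 in one arm the inflation is small.

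These figures assume alpha 0.05, equal arms of 50 and normal residuals with SD 0.208. The primary outcome, the model, the effect estimates and the omnibus test with its power are unaffected. This should be fixed, but it is not a fatal defect.

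**What to change.** Keep the omnibus F test, state alpha, and name the family of comparisons that is to be protected.

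- If the family is the three comparisons with PF alone, use closed testing. Declare an enhanced arm different from PF only if the four-arm F test, both three-arm F tests containing PF and that arm, and the pairwise t test are all significant at 5%. Power for a single effective arm at 0.114 falls from 0.71 to 0.68.
- If all six pairs are wanted, use the Fisher-Hayter critical value, |t| > 2.36 at 50 per arm, in the second step. The same power falls to 0.63.

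Either change takes a sentence or two of analysis wording and needs no change to the design, sample size or data collection. It should be made before outcome data are seen by arm. If protected LSD is kept instead, the plan should say that it controls the familywise error only when all four arms are equal.
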